## **12.0 Requirements for Participating sites and Investigators.**

All participating investigators must agree to conduct the trial in accordance with the European Clinical Trials Directive 2001/20/EC, local law, the declaration of Helsinki including all revisions, and the study protocol.

Participating sites must have the facilities and resources required for the conduct of the various defined study tests and procedures. For the specialised 11 C -metomidate scan patients will be referred to Addenbrookes Hospital Cambridge PET CT Unit.

Training materials will be provided for use of the eCRF system, plus any study-specific procedures as required.

### **12.1 Trial Sites and Numbers of Participants**

A total of 165 patients will be recruited into the study, from approx. three to six study sites within the UK depending on success on patient recruitment. Recruitment will continue until at least 70 patients have proceeded to adrenalectomy, even if we exceed a total of 165 patients being consented and undergoing investigations. This allows for some patients who may withdraw between consent and completion of investigations and/or surgery.

### **12.2 Expected duration of the clinical research.**

In total, each participant will be in the study for 2.5 years (including follow up period of 24 months). It is estimated that the total duration of the trial will be 4 years.

## **13.0 Premature site closure**

If protocol compliance is found to be poor at a particular site, or if the data quality is found to be unacceptable, efforts will be made to eradicate the problem (e.g. by additional training). However, if problems persist in spite of these efforts, premature closure of the site will be considered.

Premature closure of a site will also be considered if recruitment is particularly poor at that site.

Future follow-up and treatment of study participants from that site will be agreed by the Steering Committee.

### **13.1 Premature termination of the clinical research**

Premature termination of the trial will be considered in the event of

- new insight from other trials
- insufficient recruitment rates

The decision to terminate the trial will be taken by the Trial Steering Committee.

## **14.0 Selection of the Participants**

Patients will be identified from endocrine/ hypertension clinics

NB: All other patients with PHA however, are potential candidates for inclusion in MATCH, including those with apparently normal bilateral adrenal morphology, given that small APAs lying within the body of the adrenal may not be seen on even high resolution CT scanning.

### **14.1 Screening for eligibility**

Examination of the inclusion and exclusion criteria of potentially eligible patients will be performed using a predefined screening log. All screened patients, whether eligible or not, should be included in the screening log, with reason for ineligibility recorded as appropriate.

### **14.2 Informed Consent**

Written informed consent is required before any study-related procedures are carried out.

The patient will be sent the Patient Information Sheet in advance of their visit. The investigator/Research nurse will explain to the potential participant the purpose of the trial, any potential risks involved, the nature of the intervention, and the duration of trial participation. The patient will be informed that participation in the trial is voluntary, and that they may withdraw at any time without compromising either their future care or their relationship with their responsible physician.

The patient will be given time to consider their decision, and to discuss with the study doctor and nurse any questions about the study. If the patient is willing to participate in the trial, the study nurse will obtain the patient's informed consent: the patient will sign a consent form for study participation. The original signed consent form will be retained in the study site file, with copies added to the patient's medical notes and provided to the patient, together with the patient information sheet.

Patients unable to have cardiac MRI due to claustrophobia per se can still consent to MATCH study minus the Cardiac MRI.

### **14.3 Withdrawal of Informed Consent**

In the event that a patient wishes to withdraw consent for participation in the trial, this information will be recorded on the study conclusion page, of the eCRF noting the date of withdrawal of consent, together with the reason for withdrawal (if the patient provides that information). The patient will be reassured that their future care will not be affected by their withdrawal, and that their relationship with their responsible physician remains unaltered. The patient will be informed that any of their study data already stored will be retained, and will be used, if necessary, in the evaluation of the study drugs and for adherence to the relevant regulatory requirements.

Patients may withdraw consent for the pharmacogenetic research without affecting their participation in the study as a whole. A pharmacogenetic consent withdrawal form will be completed and signed by the patient. It will record confirmation that the sample has been destroyed.

## **15.0 Enrolment**

Before enrolment onto the study, the investigator will confirm that the patient meets all of the study inclusion criteria and none of the study exclusion criteria. Enrolment and allocation of patient ID will be carried out electronically via the eCRF and this system will prevent patients from being enrolling if they do not meet these inclusion/exclusion criteria requirements. This Patient ID will allow clinician to provide patient with order of procedures. The Patient ID acts as an identifier for return visits.

### **15.1 Violation of Eligibility criteria**

In most cases, violation of eligibility criteria is not a reason for premature withdrawal from the study. However, if, post enrolment, it is found that the patient has not been eligible at the time this must be notified to the trial CI/co-ordinator as soon as possible, and, after detailed discussion regarding the particular patient, a decision will be taken about whether they should be withdrawn from the trial.

## **16.0 Trial Procedures**

### **Home blood pressure measurements**

At several points during the trial, home blood pressure measurements are recorded. These are to be measured seated after 5 minutes rest, using the non-dominant arm. Measurements will be made using an approved and validated monitor (Microlite watch BP) or equivalent. Blood pressure readings will be taken in the morning and the evening, and the timing of these should be consistent throughout the study, ideally ~ 8.0 am and 8.0 pm – or the nearest time to these that can be constant and convenient in the individual subject on 4 consecutive days. Participants will be asked to make triplicate seated readings after 5 minutes seated rest, and to record these on a pro-forma provided. All readings will also be captured automatically by the monitor.

### **16.1 Screening and enrolment visit**

Informed Consent will be taken by physician or delegated to other members of the clinical research team. This will be taken following at least 24hrs of being in receipt of the patient information sheet. Demographic information will be recorded including gender, ethnicity, age, smoker, non-smoker, height weight. Medical history of cardiac, metabolic diseases and anything PI feels is related to hyperaldosteronism. Clinical examination. Concomitant hypertension medications will be recorded via class with a start and stop date where available.

During this visit the patient will have 3 blood pressures measured in the clinic following 5 minutes seated rest. Patients will be provided with a validated blood pressure monitor to measure home blood pressure. They will receive training on how to measure and record home blood pressures in blood pressure diary provided by a member of the clinical research team. This monitor will be used for clinic and home blood pressure measurements (Please see section above on Home blood pressure measurements)

A 12 lead electrocardiogram will be recorded. Followed by blood tests including electrolytes, , bicarbonate, creatinine, high troponin sensitivity test, brain natriuretic peptide (BNP), renin mass where available, renin activity, aldosterone and FBC. A serum HCG will be measured in child bearing potential females. Patients will be provided with x 1 24hr urine bottle for electrolytes which will be brought to baseline visit and a 10ml sample will be aliquoted for metabolomic analyses.

Inclusion and exclusion criteria will be checked with patient and recorded onto the eCRF. (Please see inclusion and exclusion criteria section 5.6)

Information and appointment details for 11C-metomidate PET CT scan and Adrenal Vein Procedures will be provided at this visit. The patient will then attend the PET CT scan and adrenal vein sampling procedures before next study visit , baseline visit.

**NB** Patients following review of PET CT scan and Adrenal Vein sampling procedure **who do not** meet the criteria for surgical intervention – adrenalectomy will attend for baseline visit, the post 2-week spironolactone /eplerenone 50mg and the post 2 week spironolactone 100mg visit. Following on from this they will have a follow-up study visit at 9-12 months. During this visit clinic blood pressures, 12 lead ECG,

### **Prior to baseline visit**

Home blood pressure measurements will be completed by the patient with 6 measurements for 4 days recorded in blood pressure diary and brought with them for the baseline visit. Patients will also be asked to attend a cardiovascular magnetic resonance (CMR) scan before or at baseline visit; this will require a washout period of 6 weeks for spironolactone/eplerenone and amiloride. The CMR will be repeated again at the 6 month visit +or- 1 month. Patients not having surgical removal of an adrenal gland will have a follow- up CMR 9-12 months following their baseline visit. Patients will be asked to arrive approximately 30 minutes before the actual scan appointment time to perform a brief assessment, complete paper work and change into a gown. A small cannula will be inserted into the patient's vein, this allows a blood sample to be taken and administration of gadolinium; it is very widely used and usually has no side effects at all; very occasionally (less than 1/100 times) it causes a temporary mild headache or nausea. The scan itself takes about forty minutes. Patients will not be included if there are any contraindications to MR imaging such as cardiac pacemakers. Patients with a contraindication to gadolinium (i.e. GFR <30 ml/min/1.73m^2). No female patients will be scanned if pregnant.

## **16.2 Baseline Visit**

During this visit the patient will have 3 blood pressures with heart rates measured in the clinic following 5 minutes seated rest. Home blood pressures taken from diary will be recorded onto eCRF

Bloods will be taken for electrolytes, bicarbonate, uric acid, creatinine, eGFR, high troponin sensitivity test, brain natriuretic peptide (BNP), renin mass, renin activity, aldosterone and serum magnesium. A serum HCG will be measured in child bearing potential females, 24 hours urine steroid profile, pharmacogenetics sample, plasma and serum samples, 24 hr Urine collection for sodium and potassium

Inclusion and exclusion criteria will be rechecked with any updates on concomitant medication.

During this visit the patient will be prescribed spironolactone/eplerenone 50mg once daily and have two return study visit at weeks 2 and 4 as below.

The aim is to have no longer than a 2 month run in period from screening visit to Baseline visit it will be up to PI interpretation and dependent on when 11 C Metomidate PET CT scan and AVS appointments. If a longer run in period is expected the CI should be consulted.

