### **16.4 Post-surgical and non-surgical follow up schedule visits at 1, 3,6,12 and 24 months.**

Patients having adrenalectomy will be followed up at 1, 3, 6, 12 and 24 months. Final follow up visit will be up to two years following adrenalectomy. During these visits patients will have 3 blood pressures with heart rates measured in the clinic following 5 minutes seated rest. Home

blood pressures taken from diary will be recorded onto eCRF. Bloods will be taken for electrolytes, bicarbonate, creatinine, high troponin sensitivity test, brain natriuretic peptide (BNP), renin mass, renin activity, aldosterone and magnesium. Renin mass done at baseline and repeated post 6 months for adrenalectomy cohort and 6-9 months for aldosterone inhibitor medication cohort. (Please refer to schedule of events table). A serum HCG will be measured in child bearing potential females. Patients having a baseline CMR in this group will have a repeat at 6 -12 months following baseline CMR

For patients not requiring an adrenalectomy there will be at least one follow up visit at 9-12 following MDT. Patients having CMR in this group at baseline will have a repeat CMR at 6-12 months following MDT. Those recruited sufficiently early in the study, will have a second follow-up visit at about 2 years following MDT.

Patients from the adrenalectomy cohort will have a repeat or 24hr urine collection for metabolomics.

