### **25.2 Data Collection and eCRF**

A Patient Identification List will be created containing personal data such as the name, gender and date of birth of all study subjects, together with their assigned study number. This list does not form part of the eCRF, and will be stored securely at the study site. This is to enable later identification of the study subjects. However, the eCRF data will be anonymous, identifying study subjects by only their assigned study number.

Section 6 details the various data recorded during the course of the trial. These data will all be entered directly into the eCRF, with the exception of the following, which will be recorded electronically and transmitted separately to the Data Centre.

- Baseline visit 12-lead ECG result

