#### **Clinical success:**

- Complete clinical success

Complete clinical success will be declared when both (a) and (b) have occurred:

(a) Normalisation of BP, defined as SBP<135 and DBP<85 mmHg on home BP; if home BP not available, then defined as SBP<140 and DBP<90 mmHg on clinic BP

(b) Not taking any antihypertensive medications

- Partial clinical success

Partial clinical success will be declared when the criteria for complete success are not met, and either (a) or (b) has occurred:

(a) reduction in BP, with no increase in antihypertensive medication, i.e. both of (i) and (ii) have occurred:

(i) BP has reduced, or has normalised, since baseline (based on home BP if available, otherwise based on clinic BP); reduction in BP defined as

- (1) a reduction in SBP of  $\geq 20$ mmHg, or
- (2) a reduction in DBP of  $\geq 10$ mmHg, with a change in SBP of  $< 20$ mmHg

(ii) the defined daily dose of antihypertensive medication being used is <150% of baseline

(b) reduction in antihypertensive medication, with no increase in BP, i.e.

(i) BP is unchanged since baseline (based on home BP if available, otherwise based on clinic BP); unchanged BP defined as

- (1) a change in SBP of <20mmHg, and
- (2) a change in DBP of <10mmHg

(ii) the defined daily dose of antihypertensive medication being used is  $\leq 50\%$  of baseline

○ Absent clinical success

An absence of clinical success will be declared when neither partial nor complete clinical success can be declared.

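### Home blood pressure enters the database from the patient's diary although the monitor captures every reading, which leaves an avoidable route to bias in the two clinical-success primary outcomes

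*Combined protocol and SAP*

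**What the plan says.** Protocol 16.0 (Home blood pressure measurements) asks patients for triplicate seated readings morning and evening on 4 consecutive days, and "to record these on a pro-forma provided". It adds: "All readings will also be captured automatically by the monitor".

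For baseline, protocol 16.2 fixes the source of the database value: "Home blood pressures taken from diary will be recorded onto eCRF". Protocol 16.4 does the same for the follow-up visits: "blood pressures taken from diary will be recorded onto eCRF". Section 16.3 (weeks 2 and 4) requires home readings but does not name their source.

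The device should be at hand in clinic. Protocol 16.1 says "This monitor will be used for clinic and home blood pressure measurements".

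Protocol 25.2 has all data entered directly into the eCRF, "with the exception of the following, which will be recorded electronically and transmitted separately to the Data Centre"; the only item listed there is the baseline 12-lead ECG. Site monitoring (26.2) is optional. Monitors are returned at the end (16.6), but no download is described. SAP section 3 defers data rules to a separate specification.

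In SAP 1.9, home BP takes priority over clinic BP. Complete clinical success needs "Normalisation of BP, defined as SBP<135 and DBP<85 mmHg on home BP", plus no antihypertensive drugs. Normalised BP is also one route to partial success. Under SAP 1.8.1, at least partial and complete clinical success are the third and fourth hierarchical primary outcomes; the first two are biochemical.

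**The concern.** The readings that reach the analysis are the ones the patient chose to write down. The protocol describes no blinding of patients: they are told if they lateralise, and they know whether they had surgery. Only the endpoint committee is described as blinded (protocol 11.0 and 24.3), and a blinded committee cannot restore readings missing from the diary.

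The reading rules leave room for selection. The schedule gives 3 × 2 × 4 = 24 readings per assessment. The protocol's primary outcome needs at least 12, and the SAP's baseline summary accepts 6. A diary that lacks its highest readings can still give a valid mean.

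If home BP at 6 months is recorded too low, some patients count as cured who were not. Under SAP 2.3.1, among operated patients, each extra cure credits the test that indicated unilateral disease and counts against the test that did not. Where only one test was positive, the planning table expects that test to be PET-CT far more often than AVS.

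**Working it through.** No figure in the documents depends on the source of home BP, so there is none to reproduce. What follows sizes the possible effect. Blood pressure means and SDs are assumptions; cell frequencies are from protocol section 33.

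**1. Shift in the home mean.**
- Suppose every patient leaves out the highest reading of each triplicate. For three normal readings the expected maximum lies 0.846 within-session SD above their mean. The mean of the other two is therefore 0.846/2 = 0.423 SD lower than the mean of three.
- For an assumed within-session SD of 4, 6 or 8 mmHg, the shift is 1.7, 2.5 or 3.4 mmHg.
- This leaves 24 − 8 = 16 readings, above both minimum counts.
- Rounding down every whole-number reading to a multiple of 5 lowers the mean by (0+1+2+3+4)/5 = 2.0 mmHg; to a multiple of 10, by (0+1+…+9)/10 = 4.5 mmHg.
- Rounding to the nearest 5 or 10 moved the mean by at most 0.14 mmHg in simulation. Only one-directional recording matters.

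**2. Share of patients moved below 135 mmHg.** Change = Φ((135 − μ + shift)/σ) − Φ((135 − μ)/σ), with assumed 6-month mean μ of 128 to 140 and between-patient SD σ of 10 to 15.
- Low end (μ 128, σ 15, shift 1.7): 3.9 points.
- Central (μ 135, σ 12.5, shift 2.5): 8 points.
- High end (μ 136, σ 10, shift 3.4): 13 points.

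**3. Effect on the paired accuracy difference.**
- PET-only unilateral: C+D+G+H = 1+10+1+9 = 21%.
- AVS-only unilateral: I+J = 0.5+3.5 = 4%.
- All operated: 21 + 4 + 30 (K+L) + 1 (M+O+P+Q) = 56%.
- Patients positive on both tests, whether to the same or opposite sides, add equally to both accuracies under the SAP rule and drop out of the difference.
- With the same cure rate c in both one-test groups, the difference is (2c − 1)(21 − 4)/56. Its slope is 2 × 17/56 = 0.61 points per point of cure.
- Central case: 8 × 0.61 = 4.9, about 5 points. If half the patients are off drugs, so that only half the shift can produce complete success: 4 × 0.61 = 2.4, about 2.5 points.

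**4. The planned analysis without AVS failures (SAP 2.3.6).**
- Removing C+D (11%) leaves PET-only 10%, AVS-only 4% and operated 45%.
- The slope is 2 × (10 − 4)/45 = 0.27.
- The central case gives 8 × 0.27 = 2.1 points, or 1.1 with half off drugs.

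**5. Comparators.** The non-inferiority margin is 17 points. With 70 operated patients, one-test-only discordance of 25/56 and a true difference near zero, the approximate 95% half-width is 1.96 × √((25/56)/70) = 15.7 points.

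**The case against.** The strongest reply is that the effect is small and rests on an extreme assumption. Every patient would have to drop the top reading of every triplicate, and nothing in the documents suggests that any do. Even then the central shift is 5 points or less, against a 17-point margin and a half-width of about 16. The planned analysis without AVS failures more than halves it. All of this stands.

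Further limits also stand:
- Clinical success remains primary only if both biochemical outcomes reach significance.
- Complete success also requires DBP below 85 and no drugs. Partial success has other routes, which dilutes the effect of the cut.
- Baseline home BP comes from the same diary, so habitual under-reporting partly cancels in SBP change, in the 20 mmHg fall and in the change-based spironolactone predictors. It does not cancel in the absolute cut.
- A diary is not wholly opaque. Omitted readings leave fewer than 24 entries, rounding shows as digit preference, and clinic BP gives a staff-attended comparison. Replaced readings stay hidden, and no rule tells anyone to look.

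A reader might infer that patients' knowledge of their treatment biases one test against the other. The documents do not support that. The primary analysis is confined to operated patients, all of whom know they had surgery, and nothing says that they learn which test prompted it. The tilt to PET-CT arises only because PET-only patients are expected to outnumber AVS-only patients.

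On the remedy, 16.0 says that readings are captured, not that they are time-stamped or kept until the visit, and it allows equivalent devices. The fix must allow for this.

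The reply does not answer the main point: the protocol provides for a device record and then leaves it unused.

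**Conclusion.** The point holds as an inexpensive improvement to the plan. The diary is the named source at baseline and follow-up, and no section uses the stored readings, even as a check. Data rules written later cannot recover readings that were never collected.

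One-directional recording could raise the share below 135 mmHg by about 4 to 13 points and move the accuracy difference towards PET-CT by about 5 points centrally (2.5 if half are off drugs), or about 2 (1) without AVS failures. These figures rest on the assumed means and SDs, on selective recording by every patient, on equal cure rates in the two one-test groups, and on the section 33 frequencies.

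A reader might go further and conclude that diary entry decides the trial's result, or that the home-BP data are unreliable. Neither follows. The illustrated shifts are well inside the margin, the biochemical primary outcomes are unaffected, and there is no evidence that misreporting occurs. The shifts matter most where a result is close, above all for superiority, which needs a lower confidence limit above 0.

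**What to change.** **Protocol 16.0, 16.2 and 16.4.** Read the monitor's stored readings at each visit. Use them as the home-BP source where the device holds identifiable readings for the scheduled days, excluding clinic and practice readings. Otherwise use the diary and flag this in the eCRF. A rule placed in 16.0 would also cover weeks 2 and 4, where no source is named. If this is impractical, the minimum is to reconcile the diary against the stored readings under a stated discrepancy rule.

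**SAP.** Derive home BP from this source, and repeat the clinical-success analyses without diary-only visits.

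**Cost.** Protocol and SAP wording, one eCRF field and a few minutes per visit. No sample size or power figure changes. For visits already completed, only what the monitors still hold can be used; overwritten readings are lost.
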